#### Statistical methods

The baseline demographic characteristics of each trial arm will be described, including age, sex, clinical history, past and present treatments and social and family history. Descriptive statistics will be used for data collected to assess the feasibility of the CBT programme, including number of logins and modules completed and the proportion of participants that used the additional resources. We will not conduct comparative statistical analysis on this portion of the data as we are underpowered to do so. Questionnaires and rating scale scores will be compared using Student’s *t* test or Wilcoxon rank sum test and summarised using means (standard deviations) or medians (inter-quartile ranges) as appropriate for continuous variables. Categorical variables will be compared using chi-squared or Fisher’s exact test and summarised as frequencies with percentages (*n*, %). All statistical analyses will be performed using R statistical software.

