### Study design

This study is a two-arm randomised feasibility study of a guided, internet-based self-help CBT programme for people with cervical dystonia, which also have elevated levels of depression and/or anxiety determined through the use of three clinically validated standardised questionnaires (Beck’s Depression Inventory, Health Anxiety Inventory, and Modified Mini Screen). All participants will undergo baseline assessments and assessments at 3 and 6 months that will take place either in the participants’ home or at our research clinic, dependent on the preference of the participant. These assessments will include a number of questionnaires relating to non-motor symptoms, including psychiatric symptoms, sleep disturbance and pain, as well as overall quality of life. A videotaped, standardised clinical examination will also be undertaken for assessment of their motor symptoms. This will allow for blinded rating of motor symptoms by two movement disorder experts. Those allocated to the control group will continue to receive only their routine clinical care for treatment of their motor symptoms, namely 3-monthly neurotoxin injections. Those allocated to the intervention will receive support setting up their account for the online CBT programme and receive guidance on how the programme works. The study schema is illustrated in Fig. 1.

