### Sample size

As this is a study aiming to determine the feasibility of using online, self-guided CBT for the management of non-motor symptoms in patients with cervical dystonia, no formal power calculation has been conducted. We aim to recruit 20 participants, with a target of randomising 10 participants into the treatment group and 10 participants into the control group.

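### Feasibility data go uncompared for lack of power, yet about 15 exploratory symptom instruments are significance-tested in the same 20 people; estimates with confidence intervals would serve the trial better

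*Protocol article*

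**What the plan says.** The Statistical methods section of the protocol article treats two kinds of data differently.

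- **Feasibility data.** "Descriptive statistics will be used for data collected to assess the feasibility of the CBT programme, including number of logins and modules completed", together with use of the optional resources. The section then adds: "We will not conduct comparative statistical analysis on this portion of the data as we are underpowered to do so".
- **Symptom data.** "Questionnaires and rating scale scores will be compared using Student’s *t* test or Wilcoxon rank sum test", with summaries as means (SD) or medians (IQR). For the rest: "Categorical variables will be compared using chi-squared or Fisher’s exact test".

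The Sample size section says that "no formal power calculation has been conducted" and gives the target: "We aim to recruit 20 participants, with a target of randomising 10 participants into the treatment group and 10 participants into the control group". On timing, Study design says: "All participants will undergo baseline assessments and assessments at 3 and 6 months". Table 4 marks every Table 1 instrument at baseline and at both outcome visits.

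The Aims and objectives section makes the symptom comparison a secondary, exploratory objective that sets participants who completed the programme against those on routine care. Outcome assessments says the measures were chosen so that they can guide later, bigger trials.

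**The concern.** Neighbouring sentences use the sample size in opposite ways. Low power is a reason not to test the feasibility data, but it does not restrain testing of the symptom scores, which come from the same 20 people and have no power calculation either. Low power bears most heavily on the symptom scores, because every one of them is measured in both arms.

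Two things are at stake. First, a long list of tests from 10 versus 10 participants can yield an isolated small p-value that is read as a sign of efficacy, or a run of large ones that is read as absence of effect. The Blinding section itself notes that participants know their allocation and that this may shift mood scores, which makes the first misreading easier. Second, a later trial needs the size of the between-arm difference, its uncertainty and the SD. The comparison that the article prescribes is a test, and where medians are used no SD is reported.

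**Working it through.** The article states no power, alpha or effect size, so there is no figure of its own to reproduce apart from the target of 20 (10 per arm), which it does not claim to be powered.

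**Inputs from the article**
- Instruments in Table 1: 5 psychiatric + 3 sleep + 4 pain + 1 quality of life + 2 motor = 15.
- Post-baseline visits: 2 (3 and 6 months).
- Participants per arm: 10.

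**Assumptions (not in the article)**
- Two-sided alpha of 0.05.
- A separate between-arm test at each visit.
- True differences of 0.5 to 0.8 SD for the power figures.
- Between-scale correlation from 0 to 0.7.

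**Number of comparisons**
- All 15 rows: 15 × 2 = 30.
- BFMDRS disability and examination combined, as Table 1 suggests: 14 × 2 = 28.
- Also leaving out Pain Time Course Patterns, which Table 1 labels qualitative: 13 × 2 = 26.
- Testing SF-36 or other subscales would raise the count; the article specifies none.

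**False positives if no scale has a true effect**
- Expected number = tests × 0.05: 26 × 0.05 = 1.3; 30 × 0.05 = 1.5. Correlation does not change this.
- Chance of at least one, independent tests = 1 − 0.95^30 = 0.785.
- Chance of at least one, correlated tests: simulation of 20,000 trials, 10 versus 10, 15 normally distributed scales at 2 visits, each compared by t test:

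| Between-scale correlation | Between-visit correlation | P(at least one p < 0.05) |
|---|---|---|
| 0 | 0 | 79% |
| 0.3 | 0.6 | 68% |
| 0.5 | 0.7 | 55% |
| 0.7 | 0.8 | 39% |

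**Power of one t test (exact, noncentral t, 18 df)**
- Noncentrality = d × √(10/2), so 0.5 × 2.236 = 1.118 and 0.8 × 2.236 = 1.789.
- 0.5 SD: 18.5%. 0.8 SD: 39.5%. Power of 80% needs a difference of 1.32 SD.
- The Harms section ends the trial when withdrawal reaches 50%. At that limit, 5 per arm, power for 0.8 SD is 20.1%.

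**Precision of an estimate**
- 95% half-width for an unadjusted difference = t(0.975, 18 df) × √(1/10 + 1/10) SD = 2.101 × 0.447 = 0.94 SD.
- This is wide, but an interval shows that width and a p-value hides it.

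**What a significant result would mean**
- False share among significant results = (1 − π) × 0.05 / [(1 − π) × 0.05 + π × power], where π is the share of scales with a true effect.
- 0.3 SD (power 9.7%), π = 0.1: 0.045 / (0.045 + 0.0097) = 82%.
- 0.8 SD (power 39.5%), π = 0.5: 0.025 / (0.025 + 0.1975) = 11%.
- The article gives neither π nor an effect size, so this share cannot be fixed.

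**The case against.** The case for leaving the section alone has several parts.

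*The article does not contradict itself.* A reader might infer that it calls itself underpowered for every group comparison and then makes them anyway. It does not: the sentence covers only the feasibility portion. This stands. What remains is reasoning applied unevenly to the same sample.

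*A significant symptom result is not thereby likely to be chance.* A reader might take the 79% that way. It is the chance of at least one false positive among 30 independent tests when nothing works. The probability that a given significant result is false ranged from 11% to 82% above, depending on inputs that the article does not supply. This stands too.

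*Low power can be a fair reason for not testing feasibility data.* One might say that there is nothing to compare, since logins, modules and tools arise only in the treatment arm. But the list in Statistical methods is not closed, the primary objective includes completing follow-up appointments, and both arms have those. For that measure the stated reason is sound.

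*The output is partly there.* Arm SDs are planned where means are used, and with the arm sizes they give an unadjusted difference and interval. That is true for those scales, but not where medians are used, and it does not yield a baseline-adjusted difference.

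*Exploratory status and the unseen documents.* The comparisons are secondary, the small sample is acknowledged under Allocation mechanism and implementation, no decision is tied to a p-value, and multiplicity rules or a named main scale may sit in an analysis plan or full protocol. This lowers the stakes and rules out criticising those as omissions. It does not reach the tests themselves, which the article prescribes.

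**Conclusion.** The point holds in a limited form. The article fixes significance tests as the method for comparing 14 or 15 symptom instruments in a sample that it regards as too small for comparing its feasibility data. At the assumed alpha and with each visit tested separately, one or two false positives are expected under no effect, while a true difference of 0.5 to 0.8 SD would usually be missed on any one scale. Neither outcome of a test is therefore much evidence about efficacy.

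Whether at least one false positive is more likely than not depends on how strongly the scales correlate: it is for independent to moderately correlated scales, but not at a between-scale correlation of 0.7. The power figures apply to the continuous scores, not to the yes/no MINI.

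This should be changed, but it does not threaten the primary feasibility objective, which is descriptive.

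**What to change.** In Statistical methods, for questionnaire and rating-scale scores:

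- Replace the between-arm tests with the between-arm difference at 3 and at 6 months, adjusted for the same instrument's baseline score, with a 95% confidence interval and the SD in each arm.
- State that no efficacy conclusion will be drawn from p-values.
- Preferably, name one depression score and one anxiety score from Table 1 as the main secondary measures and present the others as supportive. This is helpful, but the point does not depend on it.

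The sentence on power may stay for feasibility measures that both arms have, such as completion of follow-up. It would be clearer with a note that programme-use data exist only in the treatment arm and are descriptive for that reason.

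The cost is small. The baseline scores are already scheduled for every instrument and are taken before randomisation, so no new data or participants are needed. The trial gives up its p-values, and the baseline covariate takes one degree of freedom (18 to 17 with 20 completers).

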### Aims and objectives

This study is a two-arm randomised control feasibility study with the specific aim to determine the feasibility of a guided, internet-based self-help CBT programme in the management of psychiatric symptoms in patients with cervical dystonia. A secondary objective of this study is to explore the difference in non-motor and motor symptoms in patients with cervical dystonia that have completed an online CBT programme in comparison to those receiving routine clinical treatment of their motor symptoms alone.

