## Methods

### Participants, interventions and outcomes

#### Study setting

Participants will be recruited from the Global Myoclonus Dystonia Registry and Dystonia Non-Motor Symptom Study (REC 18/WM/0031 IRAS project ID: 236219). Only individuals that have consented to be contacted about future studies will be contacted. Participants meeting the inclusion criteria for this study will be sent a study flyer inviting them to enquire further if they are interested in taking part in the research. A participant information sheet (PIS) will then be sent, and the potential participant will be invited to make an appointment at their convenience for their baseline assessment. Baseline assessment will include evaluation of the participant’s motor and non-motor symptoms as well as a standardised clinical examination (Table 1; Fig. 1). Baseline demographic information will already have been collected as part of the dystonia non-motor study (Fig. 1). This appointment will also include randomisation to either the treatment or the control arm.

**Table 1 Tab1:** Study outcome assessments

Assessment	Description	Approximate duration	Type of data collected
*Psychiatric*			
Beck’s Depression Inventory	A 21-item questionnaire to identify mild mood disturbances, borderline clinical depression, moderate depression, severe depression or extreme depression. Freely available	2 min	Quantifiable
Hamilton Depression Rating Scale	A widely used and well-validated tool for measuring a patient’s depression, identifying mild, moderate, severe and very severe levels of depression	15–20 min	Quantifiable
Generalised Anxiety Disorder-7	A 7-item questionnaire to identify mild, moderate, or severe levels of anxiety. Freely available	< 1 min	Quantifiable
Hamilton Anxiety Rating Scale	A widely used and well-validated tool for measuring anxiety able to indicate mild, moderate, and severe levels of anxiety	15–20 min	Quantifiable
Mini International Neuropsychiatric Interview	An interview that covers a wide range of neuropsychiatric disorders including depression, panic disorders, anxiety, obsessive-compulsive disorder (OCD) and post-traumatic stress disorder (PTSD)	15–20 min	Yes/no
*Sleep*			
Sleep Disorders Questionnaire	A 16-item questionnaire that assesses insomnia, psychiatric disorders, circadian rhythm disorder, movement disorders and parasomnias. Freely available	1.5 min	Likert scale

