### Assignment of intervention

#### Allocation mechanism and implementation

Randomisation will be completed in a 1:1 ratio using sealed, opaque envelopes containing a computer-generated random allocation code. Envelope selection will be made by a blinded assessor and participants given the envelope to open at their baseline assessment. We aim to randomise 10 participants to the treatment arm and 10 participants to the control arm. As our sample is small, it is possible that random allocation will lead to a sample selection bias, with the full population not being represented in each arm of the study. This will need to be considered when interpreting the results.

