#### Blinding

Blinding the participant to the outcome of randomisation will not be possible due to the nature of this intervention. This could introduce bias as participants are aware if they are receiving the intervention or not, and therefore, this may affect their willingness to continue with the study, as well as their mood and state of mind. For example, participants randomised to the control arm may feel discouraged they are not receiving the intervention and therefore may withdraw from the study or demonstrate higher depression or anxiety scores. We will try to reduce this bias by conducting the baseline assessment prior to randomisation and offering participants in the control group the opportunity to try the intervention at the conclusion of the study. The assessors of the motor symptoms, undertaken by scoring of the videotaped clinical examinations, will remain blind to the participants’ random allocation.

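### The tests named for the symptom and motor scores cannot adjust for baseline scores collected before randomisation, leaving chance imbalance between arms of 10 to interpretation alone

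*Protocol article*

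**What the plan says.** The secondary objective, under Aims and objectives, reads in part: "explore the difference in non-motor and motor symptoms in patients with cervical dystonia that have completed an online CBT programme in comparison to those". The comparator is routine treatment. For this the Statistical methods section fixes the method in a sentence that begins "Questionnaires and rating scale scores will be compared using"; the tests it names are Student's t and Wilcoxon rank sum. It names no baseline covariate and no change from baseline. Its only mention of baseline is a description of demographic and clinical characteristics by arm.

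The baseline scores will exist. Under Study setting, "Baseline assessment will include evaluation of the participant’s motor and non-motor symptoms as well as a standardised clinical examination", and Table 4 lists every instrument at baseline and at both outcome visits. Under Study design, "All participants will undergo baseline assessments and assessments at 3 and 6 months". The Blinding section confirms the order, since bias is to be limited partly by "conducting the baseline assessment prior to randomisation".

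On balance, the Allocation section says: "As our sample is small, it is possible that random allocation will lead to a sample selection bias". Its only response is to bear this in mind when the results are interpreted. The target under Sample size is 10 per arm.

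**The concern.** A two-sample t test or rank sum test compares whatever score it is given and has no place for a second variable. If the arms happen to start apart on a scale, part of that gap passes into the estimated treatment difference. With 10 per arm such gaps are common, and the article raises the possibility itself. The article describes no stratification or minimisation, so the analysis is where a correction could be made, and the named tests cannot make it. The information needed is already collected at no extra burden.

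At stake are the size and precision of the between-arm differences in depression, anxiety, sleep, pain, quality of life and motor severity.

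**Working it through.** The article gives no effect size, SD, alpha or power, so there is no figure of its own to reproduce.

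**Inputs from the article:** n = 10 per arm (Sample size); baseline scored before randomisation (Blinding); the same scales at 3 and 6 months (Table 4).

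**Assumptions:** equal SDs at baseline and follow-up, normal scores, complete follow-up, two-sided alpha 0.05, an illustrative true effect of 0.8 SD, and a baseline-to-follow-up correlation rho from 0.3 to 0.8.

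**1. How often the arms start apart.** SE of a baseline mean difference = SD × √(2/n) = √(2/10) = 0.447 SD. P(|difference| > 0.5 SD) = 2 × [1 − Φ(0.5/0.447)] = 0.264, or 26% per scale. For 0.75 SD it is 9%.

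**2. What an imbalance b does to the estimate.** A follow-up-only comparison shifts by rho × b. A change-score comparison shifts in the opposite direction, by (1 − rho) × b. The shifts below are for b = 0.5 SD.

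**3. Precision and power.** The residual SD, relative to the follow-up SD, is 1 for follow-up only, √(2(1 − rho)) for change scores and √(1 − rho²) for ANCOVA. Each is multiplied by 0.447 to give the SE. ANCOVA also carries a small-sample factor √(1 + 1/16) = 1.031. At rho 0.6, for example, the change-score SE is 0.447 × √0.8 = 0.40 SD and the ANCOVA SE is 0.447 × 0.8 × 1.031 = 0.37 SD. Power for 0.8 SD is from the noncentral t distribution, with 18 df (17 for ANCOVA).

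| rho | Shift, follow-up only | Shift, change score | Power, follow-up only | Power, change score | Power, ANCOVA |
|---|---|---|---|---|---|
| 0.3 | +0.15 | −0.35 | 0.40 | 0.30 | 0.40 |
| 0.5 | +0.25 | −0.25 | 0.40 | 0.40 | 0.47 |
| 0.6 | +0.30 | −0.20 | 0.40 | 0.47 | 0.53 |
| 0.7 | +0.35 | −0.15 | 0.40 | 0.59 | 0.63 |
| 0.8 | +0.40 | −0.10 | 0.40 | 0.76 | 0.78 |

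**4. False positives.** In 100,000 simulated null trials at each of rho 0.5 and 0.7, all three methods rejected about 5% of the time overall. Among the 26% of trials with a baseline difference above 0.5 SD, rejection rates at rho 0.5 and 0.7 were 9.7% and 13.4% for follow-up only, 9.4% and 7.8% for change scores, and 4.9% at both values for ANCOVA.

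**The case against.** The strongest reply is that nothing here is invalid. A two-sample test in a randomised trial keeps its error rate over all randomisations, and step 4 confirms this. The comparison is exploratory, the article claims no power for it, and the limitation is disclosed. All of that stands. It makes this a recommendation about efficiency and conditional bias, not a charge of error.

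A second reply is that the gain may be small. At rho 0.3 there is practically none, and selecting participants for raised anxiety or depression scores could lower the correlation on some scales. This also stands, which is why the range is shown.

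A third is that a full protocol or analysis plan may add adjustment. It may, but the article does not leave the method open: it names tests that cannot adjust.

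Some stronger readings are not supported:

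- A reader might infer that the baseline scores are discarded. The article does not say whether the compared scores are follow-up values or changes. Changes would use baseline, and at moderate to high correlation would recover much of the precision. They would still leave an imbalance uncorrected, with the shift reversed.
- A reader might infer that the two follow-ups are tested separately, so that partial follow-up is wasted. The article names no time point for the tests.
- A reader might infer that these differences are meant to size a later trial. The remark about informing larger trials, under Outcome assessments, concerns the choice of outcome measures.

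**Conclusion.** The point holds in a limited form. For the continuous scales, the stated tests cannot use the pre-randomisation score as a covariate, and the article's only answer to possible imbalance is interpretation. Whether follow-up values or changes are compared, an imbalance above 0.5 SD has a 26% chance on any one scale and carries partly into the estimate.

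The 26% rests only on 10 per arm and approximate normality. The shifts and power figures depend on the assumed correlation and the illustrative 0.8 SD effect, neither of which comes from the article. The power gain over a follow-up-only test runs from nil at rho 0.3 to 0.38 (0.78 − 0.40) at rho 0.8. Against change scores, the gain at rho 0.8 is only 0.02 (0.78 − 0.76).

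The primary outcome of engagement is summarised descriptively and is untouched. The change is worth making because it is nearly free.

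**What to change.** For the continuous questionnaire and rating-scale scores, replace the t test or rank sum comparison with ANCOVA: follow-up score regressed on arm and the same scale's baseline score. Report the adjusted difference with a 95% confidence interval at 3 months and at 6 months. Keep a rank-based or bootstrap analysis as a sensitivity check for skewed scales. Leave the MINI (yes/no) and Pain Time Course Patterns (qualitative) on the categorical route already stated, since ANCOVA does not suit them.

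The cost is one sentence in the Statistical methods section and one residual degree of freedom (17 instead of 18), with no new data. If the correlation on a scale proves low, little or nothing is gained.
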